## Abstract

**Background::**

Epilepsy is a common chronic brain disorder globally affecting people of all ages, with the majority living in developing countries. The introduction of epilepsy self-management approaches to help people with epilepsy is urgently needed to influence epilepsy-related outcomes. This 2-site randomised controlled trial building on promising preliminary data is intended to explore this further.

**Methods::**

A total of 188 adult people with epilepsy (PWE) attending the neurology clinics at Mulago and Mbarara hospitals and consent to participate in the study. They will be randomised into intervention versus enhanced treatment control (eTAU) study groups. The intervention group will receive 12-week “intensive” educational sessions and a 12-week remotely accessed telephone follow-up stage. The controls will continue in their usual care supplemented by written materials on epilepsy in their preferred language and tailored to the reading level of most patients at the clinic. SMART-U consists of 2 main components: a 12-week “intensive” group format stage and a 12-week remotely accessed telephone follow-up stage. SMART-U will be assessed for acceptability, fidelity, and efficacy compared to eTAU. The primary study outcome is the mean change in cumulative past 24-week seizure frequency (24 weeks prior to the study baseline compared to the 24-week follow-up). Seizure frequency will be via self-report with corroboration by family/support system informants whenever possible. Participants will self-report their seizure frequency (numeric count) that they experienced between baseline and 13 weeks and again between 13 and 24 weeks and the mean change from baseline to 24 weeks in QOL.

**Discussion::**

The curriculum-guided Self-Management intervention for Reducing The epilepsy burden among Ugandans (SMART-U) program is anticipated to reduce the epilepsy burden seizure frequency and improve other health outcomes, including depression, functional status and health resource use.

**Trial Registration Number (TRN)::**

NCT06139198

**Date of registration::**

14^th^ November 2023

## INTRODUCTION

An estimated 70 million people worldwide carry a diagnosis of epilepsy, and 80% of them live in developing countries[1, 2]. It is estimated that about three-fourths of people with epilepsy in developing countries do not get the treatment they need[1]. Furthermore, people with epilepsy and their families frequently suffer from stigma and discrimination in their communities [1]. In Sub-Saharan Africa (SSA), inadequate care and poor control of seizures often occur, which results in an even greater number of years of potential life loss and a worse burden for patients and families with epilepsy. Poor quality of life impacts patients’ responsibility and often leads to drug non-compliance, exposure to seizure precipitants and poorer disease outcomes. Determining the quality of life among patients with epilepsy will help with developing new strategies for seizure control among these patients. Identifying clinical and demographic factors affecting the quality of life, such as lifestyle changes and early identification and management of these factors, can help improve the quality of life, seizure frequency reduction and better drug compliance.

Epilepsy self-management refers to a patient managing the treatments and day-to-day lifestyle changes associated with epilepsy and greatly influences epilepsy-related outcomes[3, 4]. Provision of care to PWE is multifaceted, including health care workers, nurses and family members. There is a scarcity of neurologists throughout sub-Saharan Africa, especially Uganda, with an estimated one neurologist for every 4 million people in East Africa[5]7. Uganda has about nine active neurologists within urban areas, with none in the rural setting. This makes the provision of care for PWE within both rural and urban settings dire. Utilisation of self-management approaches that may be provided by caregivers, nurses or other family members creates a rare opportunity to provide epilepsy care when healthcare services are difficult to come by and reduce the associated morbidity and mortality rates among this population. Self-management programs like SMART (**S**elf-**ma**nagement fo**r** people wi**t**h epilepsy and a history of negative health events) that were developed to support patients in coping with their chronic condition can improve Qol, reduce perceived stigma, and offer an opportunity to reduce epilepsy-associated mortality and morbidity [6, 7].

While there is a growing body of research to support the use of evidence-based approaches to help people with epilepsy reduce seizures and improve their health [8–10]. There is a scarcity of evidence to prove the effectiveness of self-management programs for people with epilepsy, especially in sub-Saharan Africa, with the majority of the interventions targeting increasing correct knowledge regarding epilepsy [11]. We therefore propose to evaluate the efficacy of the SMART intervention for adults with epilepsy, using a prospective design over a 24-month period in PWE in Uganda.

To advance the care of PWE, it is important to address seizures and QOL, and incorporate available mHealth support for those with poorly controlled epilepsy and limited self-management skills. There are no widely used epilepsy self-management interventions in Uganda. People living in rural communities who are underserved have also been under-studied. Use of widely available mobile phone technology (short message service/SMS) that has been minimally utilised within SSA to assist with seizure surveillance and self-management engagement among PWE.

## Methods

This prospective 2-phase study will use input from relevant stakeholders to refine the SMART-U intervention to ensure acceptability (Phase 1) and then test the effects of the intervention, reducing seizure frequency and improving other health outcomes (Phase 2).

### Study objectives

To assess the efficacy of SMART- U vs. eTAU in a prospective randomised controlled trial.

We hypothesised that individuals randomised to SMART-U will have significantly improved QOL with fewer seizures, have greater improvement in depression and functional status compared to eTAU.

To use short message service (SMS) delivered via mobile phone text to validate patient self-reported seizure occurrence and push epilepsy self-management messaging in a practical/accessible format.To obtain input from stakeholders (patients, family and clinicians) guided by an Integrated Promotion Action on Research Implementation in Health Services (i-PARIHS) framework to help establish sustainable infrastructure that will facilitate future scale-up of SMART in Uganda with epilepsy partners

### Study setting

The study population will be drawn from neurology clinics where patients with epilepsy and epilepsy-related complications receive free treatment and supportive care at Mulago and Mbarara hospitals. Mulago and Mbarara hospitals are the only hospitals currently that run regular epilepsy clinics that are supported by neurologists in Uganda and tend to provide care for severe forms that are intractable. This offers an opportunity to study this intervention.

At Mulago, patients attending the neurology clinic are referred from medical wards, while others are referred from surrounding health centers for specialised care and treatment for epilepsy. The neurology clinic runs on Wednesdays from 9 am −2 pm with an average attendance of about 5–8 patients with confirmed epilepsy. These patients are then given scheduled visits unless certain illnesses warrant an unscheduled visit. Severely ill patients were referred to the respective wards for admission and in-patient care. A total of about 20–30 patients with epilepsy are seen in the neurology clinic monthly.

Mbarara Regional Referral Hospital is a public regional referral hospital for the districts of Mbarara, Bushenyi, Ntungamo, Kiruhura, Ibanda, and Isingiro, with an official bed capacity of 600. It is located in Mbarara a teaching hospital for the Mbarara University of Science and Technology. MRRH has neurology and psychiatry clinics staffed by physicians and nurses caring for PWE. A neurologist and medical officer run the clinic, equipped with an electroencephalogram with technicians and nurses for diagnosis and care. The clinic receives about 5–10 PWE weekly and 30 PWE monthly.

### Study design

This prospective non-inferiority randomised clinical trial will be conducted at Mulago and Mbarara hospitals. Participants will be adults who meet the inclusion criteria from the epilepsy clinics at Mulago and Mbarara who will be approached to participate in the study and enrolled.

The estimated sample size for the study is 188 people with epilepsy, allowing for 20% attrition or loss by missing data, reducing the final sample to a minimum of N = 150 participants.

Based on a power analysis using G*Power 3.1.9.2121 for a 2 group by 3 time points (baseline, 13-week and 24-week follow-up) repeated measures analysis of variance (RMANOVA) with an alpha of 0.05, a power of. 80, for a sample of 150 we will be able to detect a small standardised effect size of 0.10 for the within-time effect, within the time-by-group interaction effect and a small to moderate standardised effect of 0.19 for the between-group effect.

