#### Data analysis and Data management:

The investigators at each study site will oversee data input and quality and, working with the study statistician and epidemiologist, will oversee the quantitative data analytic procedures. The CWRU data management and statistics team will also provide data management consultation as appropriate. Rigorous development of data collection forms and staff training on properly completing and checking data collection forms will reduce errors at the point of collection. Additional data management practices before and after entry into the RedCap database will identify potential problems or outlying values and catch other errors on data collection forms. Data management staff will be responsible for tracking forms entered and performing routine data checks. Analytic data sets will be prepared using SAS 9.4

Repeated Measure Analysis of Variance. The primary outcomes of interest are quality of life (QOL) and cumulative seizure frequency. Three different analytic strategies will be used to assess AIM 1. Cumulative seizure frequency will be assessed with independent samples t-tests and linear regressions, while QOL and the secondary outcomes will be examined using repeated measures analysis of variance (RMANOVA). We will examine 2 different sets of RMANOVAs.

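### The trial is labelled non-inferiority, but its hypothesis and power calculation are those of a superiority trial, and the article gives no margin

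*Protocol article*

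**What the plan says.** All references are to the protocol article.

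- **Design type (Study design):** "This prospective non-inferiority randomised clinical trial will be conducted at Mulago and Mbarara hospitals". The term appears nowhere else in the article.
- **Objective (Study objectives):** "To assess the efficacy of SMART- U vs. eTAU in a prospective randomised controlled trial".
- **Hypothesis (Study objectives):** "individuals randomised to SMART-U will have significantly improved QOL with fewer seizures, have greater improvement in depression and functional status compared to eTAU".
- **Power (Study design):** a G*Power calculation for a repeated measures ANOVA with two groups and three time points, "with an alpha of 0.05, a power of. 80, for a sample of 150". The trial is said to be able to "detect a small standardised effect size of 0.10 for the within-time effect, within the time-by-group interaction effect", and an effect of 0.19 between groups. Allowing for 20% loss, 188 are randomised.
- **Analysis (Data analysis and Data management):** "Cumulative seizure frequency will be assessed with independent samples t-tests and linear regressions". QOL and the secondary outcomes are analysed by repeated measures ANOVA.

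The article gives no margin, one-sided bound or confidence-interval rule for non-inferiority.

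**The concern.** The design label fixes the null hypothesis. In a superiority trial the null is no difference, and a non-significant result means that benefit was not shown. In a non-inferiority trial the null is that the new arm is worse by at least a margin, and a result near zero can be a positive finding. The article states the second design and then asks, and sizes the trial for, the first question. Both cannot hold.

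The label also fits the comparison poorly. SMART-U adds an orientation and hour-long group sessions led by a nurse and peer educators. eTAU is usual care with written materials and eight brief calls. Showing that the more intensive programme is not much worse than this control would not by itself establish the efficacy that the objectives claim.

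What is at stake is how a non-significant primary result would be read, and whether 188 is the right number for the design named.

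**Working it through.** **1. Is the stated sample size reproduced, and by which kind of test?**

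Inputs from Study design: N = 150 evaluable, 20% loss, alpha 0.05, power 0.80, 2 groups, m = 3 measurements, effect sizes f = 0.10 and f = 0.19. The within-person correlation rho is not given in the article. I assume 0.5, with sphericity.

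- Randomised: 150 / 0.8 = 187.5, rounded up to 188. This matches.
- Between groups: lambda = f² × N × m / (1 + (m − 1) × rho) = 0.0361 × 450 / 2 = 8.12, on 1 and 148 df. Power at f = 0.19 is 80.8%, and the effect detectable at 80% is f = 0.188. This matches the stated 0.19.
- Time-by-group interaction: lambda = f² × N × m / (1 − rho) = 0.01 × 450 / 0.5 = 9.0, on 2 and 296 df. The effect detectable at 80% is f = 0.104, which rounds to the stated 0.10. Power at exactly 0.10 is 76.6%; this is a matter of rounding and has no bearing here.
- Range: over rho from 0 to 0.8, the detectable between-group f runs from 0.133 to 0.214 and the interaction f from 0.147 down to 0.066. Of the values tried (0, 0.3, 0.5, 0.7 and 0.8), only 0.5 gives both stated figures.

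The figures are therefore those of an F-test against a null of no difference. No margin enters the calculation.

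**2. What would the same sample support as a non-inferiority trial?**

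Inputs: 150 evaluable at 1:1 gives 75 per arm if loss is equal. Further assumptions are a true difference of zero, a comparison of two means in SD units, and the normal approximation.

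- Standard error = sqrt(2 / 75) = 0.163 SD.
- Smallest margin with 80% power at one-sided 0.025: (1.96 + 0.84) × 0.163 = 0.46 SD. At one-sided 0.05 it is 0.41 SD.

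The evaluable number needed per arm is 2 × (1.96 + 0.84)² / M², rounded up. The margins M below are illustrative, since the article states none (one-sided 0.025, 80% power).

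| Assumed margin M | Per arm | Evaluable | Randomised (÷ 0.8) |
|---|---|---|---|
| 0.2 SD | 393 | 786 | 983 |
| 0.3 SD | 175 | 350 | 438 |
| 0.4 SD | 99 | 198 | 248 |
| 0.5 SD | 63 | 126 | 158 |

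Without a margin, 188 cannot be verified as a non-inferiority sample size. It would be enough only if a margin of about 0.46 SD or wider could be justified.

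**3. Effect of relabelling as superiority.** No number changes: 150 evaluable and 188 randomised stand.

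**The case against.** **It is probably a wording slip.** The term occurs once, and the Abstract, objectives, power statement and Discussion all speak of efficacy or improvement. That is likely right, and it is why the repair is small. The slip nevertheless sits in the sentence that defines the design, and results will be judged against that sentence.

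**The margin may be in a document not shown.** The article condenses a full protocol (version 2, dated 29 September 2023), and a SAP may exist. This stands: one can say only that no margin appears in this article. The contradiction does not depend on it. A margin elsewhere would leave the hypothesis and the power basis given here out of step with the design. If there is none elsewhere, the label is wrong.

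**The test names prove little.** T-tests and regression also yield the intervals that a non-inferiority analysis would use, and sidedness is not stated. A non-inferiority design can also specify a later test of superiority. Both points stand, so the finding rests on the hypothesis and the power statement.

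**A stronger reading to avoid.** A reader might infer that a null result would be presented as success. Nothing in the article says so, and the published directional hypothesis works against it. A reader might also calculate that a programme with no effect would meet an assumed 0.3 SD margin 45% of the time at 75 per arm: Phi(0.3 / 0.163 − 1.96) = 0.45. The arithmetic is correct, but when the true difference is zero, declaring non-inferiority is a correct conclusion. The 45% is power under a margin that the article does not state. It is neither an error rate nor a measure of harm to this trial.

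**Conclusion.** The design type is wrong as written: the non-inferiority label contradicts the superiority hypothesis and the superiority basis of the sample size. This does not rest on any assumed figure. It is more than clerical, because the label determines the null hypothesis and the meaning of a non-significant result, which the article leaves open.

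The numerical consequence depends on what was intended. If superiority, it is nil. If non-inferiority, 75 evaluable per arm supports only a margin of about 0.46 SD. That figure assumes 80% power, one-sided 0.025, a true difference of zero, equal loss, and a simple comparison of means that ignores the repeated measures and any skew in seizure counts. The reproduction of the power figures assumes rho = 0.5.

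**What to change.** In Study design, replace the term non-inferiority with parallel-group superiority. Add one sentence: the primary comparisons are two-sided superiority tests at alpha 0.05, and failure to reject will not be read as non-inferiority or equivalence. The full protocol and any SAP should agree with this wording. The cost is one changed term and one sentence, with no change to conduct, sample size or planned tests. It should be done before results are known, because a later correction could look driven by them.

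If non-inferiority is really intended, the change is large. The hypothesis must be rewritten, a margin stated and justified for each primary outcome, a confidence-bound rule given, and the sample size recalculated on that margin.

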### Study procedures

#### Randomisation:

Participants will be randomly assigned in a ratio of 1:1 basis to receive either SMART-U (N = 94) or eTAU (N = 94) using block randomisation. Block randomisation with a random block size of 4 to 8 consecutive patients will be performed to ensure that equal numbers of SMART and ETAU patients occur within strata and are balanced. The randomisation list will be computer-generated by staff from the CWRU Neurological and Behavioural Outcomes Centre Biostatistical Core who are not part of the study staff.

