#### Study outcomes:

The Primary outcome will be Mean change in cumulative past 24-week seizure frequency (24 weeks prior to study baseline compared to the 24-week follow-up) and Mean change from baseline to 24 weeks in QOL. Additional secondary outcomes will include Mental health comorbidity, stigma, epilepsy self-management competency, and other relevant variables, which will be assessed using validated, standardised questionnaires.

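### The only power statement is for a three-time-point RMANOVA, so its detectable effects of 0.10 and 0.19 do not describe the seizure primary, which is tested as one change score and needs about 0.46 SD

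*Protocol article*

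**What the plan says.** The sample size text (protocol article, Study design) rests on one calculation, whose model is a "2 group by 3 time points (baseline, 13-week and 24-week follow-up) repeated measures analysis of variance (RMANOVA"). The settings of that calculation are printed as "with an alpha of 0.05, a power of. 80, for a sample of 150". Two detectable effects are reported. For the repeated-measures terms the text reads "we will be able to detect a small standardised effect size of 0.10 for the within-time effect, within the time-by-group interaction effect". For the comparison of the two arms averaged over time, the figure is described as "a small to moderate standardised effect of 0.19 for the between-group effect". Neither the effect-size metric nor the correlation among the repeated measures is named. Enrolment is 188, "allowing for 20% attrition or loss by missing data, reducing the final sample to a minimum of N = 150 participants", with 94 allocated to each arm (Randomisation).

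The Study outcomes section lists two primaries. The first is "Mean change in cumulative past 24-week seizure frequency (24 weeks prior to study baseline compared to the 24-week follow-up"); the second is the change in QOL from baseline to 24 weeks. The Abstract calls the seizure outcome the primary study outcome.

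The data analysis section treats the two differently: "Cumulative seizure frequency will be assessed with independent samples t-tests and linear regressions". RMANOVA is kept for QOL and the secondary outcomes.

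**The concern.** The article prints a power basis and then a different analysis for one of its primary outcomes. The seizure outcome has two cumulative values per person, before and after baseline. These reduce to one change score compared between arms, with no time factor or time-by-group interaction. No detectable difference is given for that test.

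The wording adds to the problem. A reader who sees a small standardised effect of 0.10 will naturally think of a difference of a tenth, or perhaps a fifth, of a standard deviation between arms. If the trial can reliably find only differences near half an SD, a null seizure result may be taken as evidence against modest benefits that the trial could not have detected.

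**Working it through.** **Inputs.** Alpha 0.05, power 0.80, N = 150, 2 groups and m = 3 time points (Study design); 1:1 allocation (Randomisation), hence 75 per arm after attrition. Assumed, because not stated: a two-sided t-test, sphericity, and correlation ρ = 0.5 (the G*Power default), varied below.

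**1. Enrolment.** 150 / 0.8 = 187.5, rounded up to 188. This reproduces.

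**2. The printed RMANOVA figures.** G*Power's noncentrality is

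- interaction (and within-time): λ = N·m·f² / (1 − ρ), on F(2, 296)
- between groups: λ = N·m·f² / (1 + (m − 1)ρ), on F(1, 148)

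Solving for 80% power at N = 150:

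| ρ | interaction f | between-group f |
|---|---|---|
| 0.3 | 0.123 | 0.168 |
| 0.4 | 0.114 | 0.178 |
| 0.5 | 0.104 | 0.188 |
| 0.6 | 0.093 | 0.197 |
| 0.7 | 0.081 | 0.206 |

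At ρ = 0.5 both values round to the printed 0.10 and 0.19. The figures therefore reproduce, and they are Cohen's f.

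**3. What an interaction f of 0.10 means between arms.** For between-arm differences (δ₁, δ₂, δ₃) at the three visits, in units of the SD at one visit, the interaction f is half the population SD of the three δ values. Randomisation makes δ₁ = 0 in expectation.

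- Equal benefit at weeks 13 and 24, (0, d, d), or benefit at week 24 only, (0, 0, d): f = d/√18, so d = 0.10 × 4.243 = 0.42.
- Linear growth, (0, d/2, d): f = d/√24, so d = 0.10 × 4.899 = 0.49.

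The between-group f is half the mean of the three δ values. For (0, d, d) it is d/3, so f = 0.19 requires d = 3 × 0.19 = 0.57 at both follow-ups.

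At ρ = 0.5 the SD of a change score is √(2(1 − 0.5)) = 1 times the SD at one visit, so these values can be set beside the next result.

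**4. The seizure primary under its planned t-test.** Noncentrality is d·√(n/2), with n = 75 per arm and 148 degrees of freedom. Solving for 80% power gives d = 0.46 SD of the change score. The normal approximation agrees: (1.960 + 0.842) × √(2/75) = 0.457. With no attrition (94 per arm) it would be 0.41.

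**5. The regression alternative.** If the regression adjusts for the baseline count, with equal variances before and after, the detectable difference shrinks by √((1 + ρ)/2). In SDs of the change score:

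- ρ = 0.3: 0.46 × 0.806 = 0.37
- ρ = 0.5: 0.46 × 0.866 = 0.40
- ρ = 0.7: 0.46 × 0.922 = 0.42

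The article states neither the covariates nor ρ.

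**The case against.** **The practical gap is modest.** An interaction f of 0.10 is 0.42 to 0.49 SD, and the t-test detects 0.46 SD. The sample size is about equally adequate for either analysis, and a baseline-adjusted regression might do somewhat better. This stands, and it is why no change in enrolment follows. It does not rescue the printed numbers, which a reader cannot convert without the metric.

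**A condensed article may leave detail to the full protocol.** That is fair for an omitted correlation. Here, however, the article prints both the power basis and the analysis, and for a primary outcome they disagree.

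**Small is the conventional label for f = 0.10, and the RMANOVA does match QOL.** Both are true. The label belongs to the f scale, though, and the text calls it only a standardised effect size.

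**Seizure counts are collected at 13 and 24 weeks, so three time points could be argued.** The outcome is defined as cumulative, and the data analysis section does not put it in the RMANOVA.

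Two stronger readings are tempting and do not hold.

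- A reader might infer that the 0.10 is miscalculated, since f of exactly 0.100 at ρ = 0.5 gives 76.6% power. That takes a two-decimal figure as exact and fixes a correlation that the article does not state. At ρ of about 0.54 even exact 0.10 reaches 80%.
- A reader might convert 0.10 and 0.19 to d = 0.20 and 0.38 and report 23% and 64% power for the seizure test. That treats RMANOVA f values as two-group f values. By the translation above, an interaction f of 0.10 is at least 0.42 SD, for which the t-test has about 73% power (85% at 0.49 SD).

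**Conclusion.** Wrong as written. The stated detectable effects do not apply to the seizure primary, which has no power statement of its own. Under its planned t-test the trial has 80% power for 0.46 SD of the change score. This assumes 75 evaluable per arm, a two-sided test and the full alpha of 0.05; if alpha were halved for the two primaries, which the article does not say, the figure would be 0.51 SD. A baseline-adjusted regression could bring it to roughly 0.37 to 0.42 SD over ρ from 0.3 to 0.7, but the article gives no basis for choosing a value.

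For QOL the test and the power model agree and the arithmetic is sound at ρ = 0.5. The fault there is one of description: a detectable difference of about 0.42 to 0.49 SD at week 24 is presented as small. None of this shows that the trial is too small.

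**What to change.** Keep 188 participants and rewrite the power paragraph.

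- **Seizures:** state that, with 75 evaluable participants per arm and two-sided alpha 0.05, the t-test on change in cumulative 24-week seizure frequency has 80% power for a between-arm difference of 0.46 SD of that change. If the baseline-adjusted regression is to be the main analysis, say so and give the assumed correlation with the resulting figure.
- **RMANOVA:** name Cohen's f as the metric for 0.10 and 0.19, and state the correlation entered in G*Power.
- **QOL:** express the interaction figure as a between-arm SD difference at week 24 (0.42 to 0.49, with the assumed time course) and remove the word small.

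The cost is one rewritten paragraph and a stated sensitivity that looks less favourable. It needs no extra participants and no change to the analysis.
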